## Abstract

**Background:**

Around 10% of school-aged children experience mental health difficulties. Many more are ‘vulnerable’: experiencing emotional and/or behavioural problems reaching clinical levels, and thus at greatest risk of future mental illness. The trial aim is to evaluate the effectiveness of the CUES for schools programme in reducing emotional and behavioural problems in vulnerable children.

**Methods:**

The “CUES for Schools” study is a multicentre cluster randomised controlled trial in primary schools in south east England. Schools will be randomised to receive the usual school curriculum, or the CUES programme (1:1). We aim to enrol 74 schools (5550 children including 2220 vulnerable children). CUES is a whole-class teacher-facilitated interactive digital cognitive-behavioural intervention, delivered as 24 short (20-min) modules over 12 weeks, targeting emotional/behavioural regulation skills. Children self-report emotional/behavioural problems at baseline, 8, and 16 weeks, and wellbeing and cognitive vulnerability at 0 and 16 weeks. Adverse events are assessed at 8 and 16 weeks. Teachers rate classroom behaviour at baseline and 16 weeks. School senior leadership teams and individual teachers consent to involvement in the study; parents can opt their child out of CUES sessions, assessments, or research. Children can similarly opt out and assent to research participation. The primary objective of this trial is to evaluate the effectiveness of CUES for schools compared to the usual school curriculum in improving emotional/behavioural problems for vulnerable Year 4 (8–9 years old) children at 16 weeks post-randomisation, as measured using a standardised questionnaire designed for primary schools. The secondary objective is to investigate the impact of the CUES for schools programme on both vulnerable and non-vulnerable children on wellbeing and teacher-rated classroom behaviour.

**Discussion:**

The study will show whether CUES for schools is more effective than the usual curriculum in reducing emotional and behavioural problems in vulnerable Year 4 children, and thus reducing the risk of mental health difficulties in later adolescent and adult life. As a digital, teacher-facilitated intervention, CUES for schools can be readily implemented, at minimal cost. If effective, CUES for schools therefore has the potential to reduce the impact of emotional/behavioural difficulties on children’s learning, behaviour, and relationships and the burden of future mental health morbidity.

**Trial registration:**

Trial Registration ISRCTN11445338. Registered on September 12, 2022.

## Administrative information

Note: the numbers in curly brackets in this protocol refer to SPIRIT checklist item numbers. The order of the items has been modified to group similar items (see http://www.equator-network.org/reporting-guidelines/spirit-2013-statement-defining-standard-protocol-items-for-clinical-trials/).

## Introduction

### Background and rationale {6a}

Three quarters of all adult mental illness onsets before late adolescence (25 years), and half by the age of 15 years, with mental health and substance use accounting for a quarter of disease burden across childhood and adolescence [1, 2]. Globally, around 10% of school-aged children experience mental health problems, such as anxiety and depression; a fifth experience significant emotional and/or behavioural difficulties which impact on learning, behaviour, social relationships, and motivation and increase vulnerability to mental health difficulties in later adolescence and adult life [3]. UK government reports for England suggest higher rates, increasing since 2017 from 10 to 16% [4]. In our recent work, nearly half of 7–10-year olds in London were ‘vulnerable’, herein defined as self-reporting emotional/behavioural problems at levels typical of clinical populations [5, 6].

Reducing vulnerability to future mental ill-health by targeting emotional/behavioural problems in childhood, building resilience and improving wellbeing, has been a global health priority over the last decade [3]. In the context of limited capacity in and access to child and adolescent mental health services (CAMHS), school-based mental wellbeing promotion initiatives have burgeoned, and, in England, become a mandatory part of curricula [7, 8]. Research outcomes are mixed, with the best evidence for cognitive behavioural approaches, delivered to whole classes, which facilitates peer support and normalising without labelling vulnerable children [9–11]. In practice, outcomes continue to be poor, particularly for more vulnerable children: further development of interventions that are readily implementable longer-term is needed [12, 13].

The CUES for schools programme aims to address this need, as a teacher-facilitated, interactive digital platform version of the mental health professional face-to-face delivered CUES-Ed intervention, a cognitive-behavioural whole class approach for 7–10-year olds [5, 6]. CUES is not an acronym in this context; it references the programme content concerning noticing cues to our own emotional state. CUES is designed to reduce emotional/behavioural problems, particularly for vulnerable children, by promoting emotional literacy and emotional/behavioural regulation, both linked with childhood social and academic functioning [14, 15]. CUES also aims to reduce cognitive vulnerability to mental health problems by reducing stigma and promoting flexible thinking and normalising explanations of unusual perceptual experiences, such as seeing or hearing things which others cannot [16].

Development of the CUES programme has required a highly iterative process with children and teachers to ensure a robust and accessible resource. Each learning objective has been translated into a combination of real-life video, animation, plus interactive exercises. As in the original programme, children receive a hard copy workbook and home access to the CUES website.

Service evaluation [5, 6] showed high rates of acceptability by children and teachers and small improvements on whole class wellbeing. Importantly, children identified as vulnerable benefited following CUES-Ed, which motivated its use as our proposed feasibility trial. In this, the CUES for schools programme was found feasible, as we randomised 11 schools (1:1) and 299 schoolchildren to receive CUES, and 6 schools and 419 schoolchildren to the usual curriculum (waitlist control) ([17], ISRCTN12486546]), as well as a suggested signal in vulnerable children consistent with the service evaluation.

The aim of this protocol is to describe the methods underpinning the CUES for schools study. The study aim is to evaluate the effectiveness of the CUES for schools intervention, as an adjunct to the usual school curriculum, compared to the usual school curriculum alone, in reducing emotional and behavioural problems in vulnerable Year 4 school children in England, receiving the intervention as part of a whole class.

### Objectives {7}

#### Primary objective

The primary objective of this trial is to evaluate the effectiveness of CUES for schools compared to the usual school curriculum in improving emotional/behavioural problems for vulnerable Year 4 children at 16 weeks post-randomisation, as measured using the Me & My Feelings total score (M&MF) [17]. This objective relates to the primary sub-population of children meeting the threshold for vulnerability on the emotional and/or behavioural problems subscales of the M&MF (M&MF-E > 9 and/or M&MF-B > 5) at baseline assessment.

#### Secondary objectives

Secondary aims will be to investigate the impact of the CUES for schools intervention on secondary wellbeing outcomes and on teacher-rated classroom behaviour, as well as exploring the effectiveness of CUES for schools across the wider school population (both vulnerable and non-vulnerable).

### Trial design {8}

The design will be a 16-week, multicentre, parallel-group cluster RCT with random allocation of schools to either CUES or the usual curriculum (1:1) to reduce emotional and behavioural problems in vulnerable Year 4 children. The framework of the trial is superiority.

This protocol (Version 1, 12th September 2022) has been written according to the SPIRIT 2013 guidance. The study obtained ethical approval from King’s College London Research Ethics Committee (KCL REC ref. HR/DP-21/22–28,344) on 19th August 2022.

Enrolment will start in October 2022 and is planned to end in February 2023.

## Methods: participants, interventions and outcomes

### Study setting {9}

We will approach the Senior Leadership Teams (SLTs, i.e. the Headteacher and their nominated deputies) of primary schools in inner and outer London and, if needed, extend recruitment to the home counties (the local administrative areas proximal to outer London). Schools will be mainstream (open to all children with no special entry criteria) and funded by local authorities.

### Eligibility criteria {10}

#### Inclusion criteria

The school and child inclusion criteria are shown as follows:

##### School (cluster) inclusion criteria

Funded by the local authority/borough (i.e. a state school, providing education free at the point of delivery to children resident in or with a connection to the local area), providing mainstream education.

##### In London or the home counties

With an intake at Year 4 (children aged 8–9 years) and Year 5 (children aged 9–10 years), so that waitlist control schools, delivering the intervention after completing the 16-week assessment, will definitely have time to deliver the intervention.

##### Child

All children in Year 4 (aged 8–9 years).

#### Exclusion criteria

##### Child

None.

### Who will take informed consent? {26a}

We will approach schools to express interest in participating around 6 weeks before the anticipated randomisation date.

SLTs will be asked for their agreement to participate on behalf of their school. SLTs will consult with teachers of Year 4 children before agreeing to participate, to ensure willingness to deliver the intervention. Once SLTs have consented on behalf of the school, we will liaise directly with teachers to ask formally for their separate consent. Once the SLT and teachers have consented, the school will be considered to be participating in the study.

Information sheets will inform parents of the school’s decision to deliver the intervention as part of a randomised controlled study, and to complete evaluation measures. Parents will be offered the option to remove their child from the CUES teaching and assessments if they wish, by liaising directly with the school.

Parents will be offered the opportunity to opt out of their child’s self-report measures being used for a research purpose. This will be by direct communication with the research team, using an online form. Once parent information sheets have been sent out, children will be told about the study by their teacher, using a video from the study team to standardise the information provided across all schools.

Trained research workers will complete assessments with children and teachers at T0, T1, and T2 (see Table 1).

**Table 1 Tab1:** Participant timeline

	Engagement with school	Baseline 0-weeks (T0)	Intervention	8-weeks (T1)	16-weeks (T2)
Senior Leadership Team consent	X				
Teacher liaison/consent	X				
Parent letter, opt-out	X				
Child assent		X			
Randomisation			X		
Intervention		➔	➔	➔	➔
Assessment measures					
Primary outcome: Child-rated emotional and behavioural problems (Me and My Feelings)		X		X	X
Secondary outcome: Child-rated wellbeing (Child Outcome Rating Scale)		X			X
Secondary outcome: Teacher-rated outcomes		X			X
Secondary outcome: Child-rated workbook measures		X			X

### Additional consent provisions for collection and use of participant data and biological specimens {26b}

N/a there will be no biological specimens collected in this study.

## Interventions

### Explanation for the choice of comparators {6b}

*The usual school curriculum* for emotional and social learning will be delivered to all children, irrespective of receipt of CUES. The usual school curriculum is nationally set, with limited scope for variation by school. We will ask school senior leadership how they teach these aspects of the curriculum and record what is delivered in the usual curriculum, but will not interfere with usual delivery. In particular, as CUES will not comprise additional hours of teaching, we will record any difference arising in the routine curriculum delivered in intervention and waitlist (WL) control schools.

### Intervention description {11a}

*CUES* comprises seven modules, with 24 lessons delivered over 12 weeks (within a 16-week window), in sessions of 20 min, two or three times/week. Schools will be asked to incorporate CUES into their social and emotional learning provision, so children do not have additional time in the classroom. The programme consists of digital interactive sessions. Teachers guide their class through the sessions using the content and interactivities that are part of the package. The package incorporates branding and characters designed to be appealing and engaging, in a mix of animation and video. Children in the intervention arm will receive CUES straight away. Children in the WL arm will receive CUES later in the term or in the following academic year.

For schools allocated to the CUES arm, teachers will watch the instructional video, and start the CUES programme. CUES delivery should start within 2 weeks of randomisation and proceed at an hour each week. There are 12 h of teaching to deliver within the 16-week window. Measures will be completed at baseline, T1 (8 weeks, primary outcome only) and T2 (16 weeks) in both arms.

The end of the trial will be defined as the last follow-up assessment at T2. WL participants will then receive CUES, at a time suitable in the context of the usual curriculum. This will not be part of the outcomes of the study and children will not be asked to complete any further measures.

### Criteria for discontinuing or modifying allocated interventions {11b}

Not applicable. We will not be reviewing interim data and extensive piloting has revealed no safety issues. Discontinuation would only be at the request of the school, and would be a withdrawal from the study.

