### Sample size {14}

In our feasibility trial [19], we found an effect size of 0.2. Assuming a type-1 error = 0.05 (two-sided test) with 90% power and an intraclass coefficient (ICC) of 0.025, a total of 68 schools are needed to be included in the analysis population, each with 25 vulnerable children. After accounting for a loss to follow-up at 5% of schools, and then a loss of 15% of vulnerable children, we will randomise 74 schools (1:1) to enrol 2220 vulnerable children.

In typical schools, there are approximately 75 Year 4 children, of which 40% are vulnerable, thus 30 vulnerable children per school. Approximately 5550 children will be enrolled in total, including 2220 vulnerable and 3330 non-vulnerable.

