## Statistical methods

### Statistical methods for primary and secondary outcomes {20a}

Prior to the database lock a statistical analysis plan (SAP) will be developed following King’s Clinical Trials Unit (KCTU) Standard Operating procedures (KCTU ST:02 — developing a statistical analysis plan) and approved by the trial team and the independent TSC chair statistician.

Briefly, all statistical analyses will adopt an intention-to-treat principle (ITT) whereby all schoolchildren will be analysed in accordance to the condition in which they were randomised, with this being a modified ITT for the primary outcome to allow for the inclusion of only the vulnerable sub-sample. All analyses will be conducted after data collection has been completed and pre-processed, the SAP has been signed off and the database has been locked. All variables will first be summarised using descriptive statistics (e.g. means and SDs for normally distributed continuous variables, and median and interquartile ranges skewed continuous data), prior to inferential analyses, and M&MF descriptives will be further sub-divided to confirm the proportion of children meeting the criteria for vulnerability at each timepoint.

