#### Withdrawal of participants

Schools will have the right to withdraw from the study at any time up until the start of delivery for any reason. Once delivery has begun, both children and parents will also be involved and a school opt-out will need to take their wellbeing and expectations into account.

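### Treating a school's discontinuation of CUES as withdrawal from the study can remove follow-up outcomes in the CUES arm only, which undercuts the as-randomised analysis

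*Protocol article*

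**What the plan says.** Section {11b} of the protocol article, on discontinuing allocated interventions, is marked not applicable but then fixes a rule: "Discontinuation would only be at the request of the school, and would be a withdrawal from the study".

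The section on withdrawal of participants adds: "Schools will have the right to withdraw from the study at any time up until the start of delivery for any reason". After that point, "a school opt-out will need to take their wellbeing and expectations into account".

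Delivery starts at different times in the two arms. For CUES schools, the intervention description {11a} says "CUES delivery should start within 2 weeks of randomisation". For waitlist schools, the same section places delivery after the end of the trial ("WL participants will then receive CUES, at a time suitable in the context of the usual curriculum"), and the school inclusion criteria refer to "waitlist control schools, delivering the intervention after completing the 16-week assessment".

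Section {20a} states the analysis principle: "all schoolchildren will be analysed in accordance to the condition in which they were randomised". The one reason it gives for calling the primary analysis modified intention-to-treat is the restriction to vulnerable children. The primary outcome analysis and section {20c} then limit the population to children with at least one follow-up measurement. The secondary outcome analysis omits children without follow-up data. Section {18b} reports no plans to promote retention, and the sample size section {14} allows for school loss without distinguishing the arms ("After accounting for a loss to follow-up at 5% of schools").

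**The concern.** An as-randomised analysis needs outcomes from schools whether or not they carry on with the intervention. Section {11b} joins two separate events: a school ceasing to deliver CUES, and a school leaving the study. Nothing in the article says that the 8-week (T1) and 16-week (T2) measures continue in a school that stops.

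Only one arm has an intervention to stop during follow-up. The loss that this rule permits is therefore confined to CUES schools and is prompted by their experience of CUES. If such schools would have done worse than those that continued, the observed contrast moves towards the effect among schools that kept delivering, while still being reported as intention-to-treat.

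The withdrawal section adds a second dependence on arm. The unconditional right runs until delivery starts, and delivery starts on either side of the follow-up period depending on allocation.

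Outcomes that were never collected cannot be recovered at analysis, so this has to be settled in the protocol and not in the statistical analysis plan.

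**Working it through.** **1. Who can trigger each rule during follow-up**

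| Rule | CUES schools | Waitlist schools |
|---|---|---|
| Discontinuing CUES counts as study withdrawal ({11b}) | Possible from start of delivery to T2 | Not possible before T2: nothing to discontinue |
| Unconditional right to withdraw (withdrawal section, with {11a} and the inclusion criteria) | Up to about 2 weeks after randomisation, then qualified | All of follow-up: 16 weeks nominal, 14 to 20 with the T2 assessment window in {18a} |

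The first row can remove CUES schools only. The second makes leaving easier for waitlist schools. The two routes act in opposite arms.

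**2. What happens to the data of a school that leaves**

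- Before T1: its children have no follow-up measurement and are excluded from the primary analysis.
- Between T1 and T2: its children stay in the primary model through their 8-week scores. Their 16-week outcome, which is the primary endpoint, is handled by maximum likelihood and so rests on missing at random.
- Any time before T2: its children are lost to the secondary outcomes, which are analysed at 16 weeks only.

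**3. The plan's own sample size**

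Inputs from {14}: effect 0.2, two-sided alpha 0.05, power 90%, ICC 0.025, 25 vulnerable children per school, losses of 5% of schools and 15% of children.

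- Children per arm without clustering: 2 × (1.960 + 1.282)² / 0.2² = 525.4, rounded up to 526.
- Design effect: 1 + (25 − 1) × 0.025 = 1.6.
- Schools per arm: 526 × 1.6 / 25 = 33.7, so 34, or 68 in total. This matches the plan.
- School loss: 68 / 0.95 = 71.6, so 72; the plan's 74 is slightly conservative.
- Child loss: 25 / 0.85 = 29.4, so 30 per school; 74 × 30 = 2220. This matches the plan.

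The sample size contains no arithmetic error.

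**4. Illustrative bias**

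The documents give neither the number of schools that would stop nor their outcomes. Assumptions: the whole 5% school allowance falls in the CUES arm, those schools leave before T1, and they lack the planned 0.2 SD benefit that the other CUES schools have.

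- Schools lost: 0.05 × 74 = 3.7, about 4 of the 37 in the arm.
- Bias = share lost × difference = (4/37) × 0.2 = 0.022 SD.
- Relative to the target effect: 0.022 / 0.2 = 11%.
- Standard error with 33 v 37 schools: √[(1.6/25) × (1/33 + 1/37)] = 0.061 SD, so the bias is 0.022 / 0.061 = 0.36 of a standard error.

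Over a wider assumed range, with 5% to 20% of CUES schools lost and a difference of 0.1 to 0.3 SD, the bias runs from 0.05 × 0.1 = 0.005 SD to 0.20 × 0.3 = 0.06 SD, or 2.5% to 30% of the target. The ICC puts the between-school SD at √0.025 = 0.16, so a difference of 0.3 SD is already about 1.9 between-school SDs. The upper end is therefore a stretch.

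**5. Power**

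Normal approximation, 25 children per school: 92.5% with 37 v 37 schools and 91.0% with 33 v 37. The issue is bias, not power.

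**The case against.** Section {11b} is one line in a condensed article. It does not say that assessments cease or that collected data are discarded, and {11a} says measures are completed at all three time points in both arms. Both points are true, but a school that has withdrawn from the study is ordinarily not assessed further, and no sentence provides otherwise.

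A reader might infer that any CUES school which delivers poorly disappears from the data. The text does not support that. Sections {11c} and {12} record sessions completed and whether each child attended at least half, so under-delivering schools are measured. The rule applies only when a school asks to discontinue.

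A reader might also infer that waitlist schools may leave freely while CUES schools are locked in. The withdrawal section sets no arm-specific rule; the difference appears only when it is read with the delivery timetable. After delivery starts, opting out is qualified, not ended.

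The strongest inference, that the trial will lose schools selectively and in favour of CUES, also fails. Selective loss is a risk. The two routes oppose each other, and the text fixes neither the net imbalance nor its direction. Equal numbers lost would not guarantee that the biases cancel, because schools would leave for different reasons in each arm.

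Finally, the restriction to children with follow-up data is openly stated, and no child is reassigned. The rule therefore undercuts the as-randomised principle without formally contradicting it. None of this removes the core point: stopping the intervention is defined as leaving the study, and only one arm can do so during follow-up.

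**Conclusion.** The point holds as a flaw in a stated rule. Section {11b} allows T1 and T2 outcomes to be lost in the CUES arm alone, for reasons linked to the intervention, and the planned analysis cannot fully repair that. The unequal length of the unconditional withdrawal right is a secondary weakness that follows from reading several sections together.

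The likely size is modest. Under the stated assumptions (4 of 37 CUES schools lost entirely, each lacking the 0.2 SD benefit), the effect would be overstated by about 0.022 SD. The primary-outcome bias could be smaller if some of those schools left after T1, because their 8-week data would stay in the model. Larger figures, such as those from stopping schools doing 0.3 or 0.5 SD worse, are hard to square with the protocol's ICC: they would lie about 1.9 or 3.2 between-school SDs from the rest. The true number of schools affected and the net direction across both routes are unknown. Correction is still worthwhile because it is cheap and must come before outcomes go uncollected.

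**What to change.** In {11b} and in the withdrawal section:

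- Separate stopping CUES delivery, or not starting it, from withdrawing from data collection.
- State that a school which stops or never starts is asked to complete T1 and T2 and is analysed as randomised, unless it separately withdraws from assessment. Assessment cannot be imposed on a school that withdraws from it, so the wording should be a request.
- Word the right to withdraw from assessment identically in both arms, timed from randomisation and not from the start of delivery.
- Reconcile these two sections with the analysis principle in {20a} and the population definition in {20c}.

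The same statement should go into the agreement signed by school senior leadership. When a school may stop delivering is left unchanged. The cost is protocol wording and a line in the school agreement; the T1 and T2 assessments are already planned in both arms.
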